# Evaluating the efficacy of dexamethasone in the treatment of patients with persistent acute respiratory distress syndrome: study protocol for a randomized controlled trial

**DOI:** 10.1186/s13063-016-1456-4

**Published:** 2016-07-22

**Keywords:** Acute respiratory distress syndrome, Dexamethasone, Corticoids, Positive end-expiratory pressure, Lung-protective ventilation

## Abstract

**Background:**

Although much has evolved in our understanding of the pathogenesis and factors affecting outcome of patients with acute respiratory distress syndrome (ARDS), still there is no specific pharmacologic treatment for ARDS. Several clinical trials have evaluated the utility of corticoids but none of them has demonstrated a definitive benefit due to small sample sizes, selection bias, patient heterogeneity, and time of initiation of treatment or duration of therapy. We postulated that adjunctive treatment of persistent ARDS with intravenous dexamethasone might change the pulmonary and systemic inflammatory response and thereby reduce morbidity, leading to a decrease in duration of mechanical ventilation and a decrease in mortality.

**Methods/design:**

This is a prospective, multicenter, randomized, controlled trial in 314 patients with persistent moderate/severe ARDS. Persistent ARDS is defined as maintaining a PaO_2_/FiO_2_ ≤ 200 mmHg on PEEP ≥ 10 cmH_2_O and FiO_2_ ≥ 0.5 after 24 hours of routine intensive care. Eligible patients will be randomly allocated to two arms: (i) conventional treatment without dexamethasone, (ii) conventional treatment plus dexamethasone. Patients in the dexamethasone group will be treated with a daily dose of 20 mg iv from day 1 to day 5, and 10 mg iv from day 6 to day 10. Primary outcome is the number of ventilator-free days, defined as days alive and free from mechanical ventilation at day 28 after intubation. Secondary outcome is all-cause mortality at day 60 after enrollment.

**Discussion:**

This study will be the largest randomized controlled clinical trial to assess the role of dexamethasone in patients with persistent ARDS.

**Trial registration:**

Registered on 21 November 2012 as DEXA-ARDS at ClinicalTrials.gov website (NCT01731795).

**Electronic supplementary material:**

The online version of this article (doi:10.1186/s13063-016-1456-4) contains supplementary material, which is available to authorized users.

## Background

The acute respiratory distress syndrome (ARDS) is an inflammatory disease process of the lungs as a response to both direct and indirect insults, characterized clinically by severe hypoxemia, reduced lung compliance, and bilateral radiographic infiltrates [1]. The mechanisms by which a wide variety of insults can lead to this syndrome are not clear. Although much has evolved in our understanding of its pathogenesis and factors affecting patient outcome, still there is no specific pharmacologic treatment for ARDS. Despite advances in supportive measures, ARDS has a mortality rate of about 40–50 % in most series [2]. Patients with ARDS invariably require mechanical ventilation (MV) to decrease the work of breathing and to improve oxygen transport. To date the only proven, widely accepted method of MV for ARDS is “lung-protective ventilation” using a low tidal volume (V_T_) strategy plus moderate to high levels of positive end-expiratory pressure (PEEP).

Corticoids seemed to be an ideal therapy for the acute lung injury in ARDS, given their potent anti-inflammatory and antifibrotic properties [3]. They switch off genes that encode pro-inflammatory cytokines and switch on genes that encode anti-inflammatory cytokines. It has been reported that low doses of corticosteroids prevent an extended cytokine response and might accelerate the resolution of pulmonary and systemic inflammation in pneumonia [4]. Several clinical trials have evaluated the utility of methylprednisolone in ARDS [5–15]. None of them has demonstrated a definitive benefit due to small sample sizes, selection bias, patient heterogeneity, and time of initiation of treatment or duration of therapy. The ARDS Network performed the largest randomized trial of methylprednisolone versus placebo in 180 patients with ARDS of at least 7 days duration [13]. Although there was no survival benefit in the steroid group, methylprednisolone increased the number of ventilator-free days (VFDs) and intensive care unit (ICU)-free days during the first month. Also, a meta-analysis of selected trials showed that prolonged administration of systemic steroids is associated with favorable outcomes and survival benefit when given before day 14 of ARDS [16].

Despite these disappointing trial results, great interest remains in the use of corticosteroids for the salvage of ARDS patients in the early phase of their disease process, a situation that has not been evaluated in most published trials. Paradoxically, these hormones are given as adjunctive therapy in patients with septic shock [17]. We postulated that adjunctive treatment of persistent ARDS with dexamethasone might change the pulmonary and systemic inflammatory response and thereby reduce morbidity, leading to a decrease in duration of MV and to a decrease in mortality.

## Methods/design

### Justification of the study

Currently, there is no proven pharmacologic treatment for patients with ARDS. Protective MV is the most important aspect of supportive care of ARDS patients. Dexamethasone has never been evaluated in ARDS in a randomized controlled fashion. However, dexamethasone has potent anti-inflammatory effects and weak mineralocorticoid effects compared with other corticosteroids [18]. It is 20 to 30 times more potent than the naturally occurring hormone cortisol and four to five times more potent than prednisone [3]. Dexamethasone has a long-lasting effect, allowing for a once-a-day regimen [18]. Whether addition of dexamethasone to conventional supportive treatment benefits ARDS patients is unknown, it has been used in patients with pneumonia [18], septic shock [19], meningitis [20], and other causes of ARDS [21].

We justify the need of our study based on the positive results of two recent clinical trials: (i) Meijvis et al. [18] showed that dexamethasone (5 mg/day) for 4 days was able to reduce length of hospital stay in 304 patients with bacterial pneumonia when added to conventional treatment; (ii) Azoulay et al. [21] showed that dexamethasone (10 mg/6 h), when added to chemotherapy and conventional ICU management, caused less respiratory deterioration and lower ICU mortality in 40 patients with acute lung injury resulting from leukemia. Our goal is to examine the effects of dexamethasone on length of MV (assessed by number of ventilator-free days) and on 60-day mortality, in patients admitted into a network of Spanish intensive care units (ICUs) who still meet ARDS criteria at 24 hours after ARDS onset despite routine intensive care management.

### Study design

The DEXA-ARDS study is a prospective, multicenter, randomized, controlled trial in 314 patients with persistent ARDS admitted into a network of 18 ICUs from university and community hospitals in Spain (Appendix 1).

The trial has been designed in accordance with the fundamental principles established in the Declaration of Helsinki, the Convention of the European Council related to human rights and biomedicine, and the Universal Declaration of UNESCO on the human genome and human rights, and within the requirements established by Spanish legislation in the field of biomedical research, the protection of personal data, and bioethics, which was classified by the Spanish Agency of Drugs and Medical Devices (Agencia Española del Medicamento y Productos Sanitarios) as a clinical randomized study with drugs on 21 November 2012 and registered on 21 November 2012 at http:/www.clinicaltrials.gov with identification no. NCT01731795. The study was approved by the referral Ethics Committee (Hospital Clínico Universitario de Valencia, Valencia, Spain) and the institutional review boards of all participating hospitals (Additional file 1). For inclusion into the study, signed written informed consent from the patient or the patient’s personal legal representative will be provided (Additional file 2). See Additional file 3 for the SPIRIT checklist of the study protocol.

### Study population

To be eligible for inclusion into this study (day 0), each patient (male or female) must fulfill the following inclusion criteria during screening and prior to enrollment into the study: age ≥18 years, be intubated and mechanically ventilated, and have acute onset of ARDS, as defined by the American-European Consensus Conference (AECC) criteria for ARDS [22] or as moderate/severe ARDS by the Berlin criteria [23], which include: (i) having an initiating clinical condition (pneumonia, aspiration, inhalation injury, sepsis, trauma, acute pancreatitis, etc.); bilateral infiltrates on frontal chest radiograph, (ii) absence of left atrial hypertension, a pulmonary capillary wedge pressure less than 18 mmHg, or no clinical signs of left heart failure, (iii) hypoxemia (as defined by a ratio between partial pressure of oxygen in arterial blood and fraction of inspired oxygen (PaO_2_/FIO_2_) ≤ 200 mmHg on PEEP ≥ 5 cmH_2_O, regardless of FiO_2_). Patients will be excluded from study participation if any of the following are present: pregnancy or active lactation, enrollment in another experimental treatment protocol, brain death, terminal-stage cancer or other terminal disease, having do-not-resuscitate orders, immunocompromised, receiving corticosteroids or immunosuppressive drugs, more than 24 hours elapsed after initially meeting the ARDS criteria before consent and results of initial standard ventilator settings could be obtained, severe chronic obstructive pulmonary disease, or congestive heart failure.

### Enrollment into the study and randomization

For the present study, onset of ARDS was defined as the day and time in which the patient first met ARDS criteria [22, 23]. Screened patients will be considered for enrollment immediately prior to randomization and to the first dose of study medication on day 1 if they still meet the ARDS inclusion criteria at 24 hours after ARDS onset, assessed on standard ventilator settings. Arterial blood gases and hemodynamic and data will be obtained on the following mandatory standard ventilator settings: volume assist/control mode, V_T_ 7 ml/kg predicted body weight (PBW), inspiratory:expiratory (I:E) time ratio 1:1, ventilator rate to maintain a partial pressure of carbon dioxide (PaCO_2_) of 35 to 50 mm Hg, on FiO_2_ ≥ 0.5 and PEEP ≥ 10 cmH_2_O) [24]. If under these ventilator settings, the PaO_2_/FiO_2_ is ≤ 200 mmHg, the patient will be eligible for randomization.

Eligible, informed consented patients will be randomly allocated to two arms: (i) conventional treatment without dexamethasone and (ii) conventional treatment plus dexamethasone. Randomization will be performed by blocks of ten opaque, sealed envelopes sent to each participating ICU, according to a computer-generated random-number table. Randomization will be based on one-to-one allocation of prenumbered envelopes. As requested, a second block of ten sealed envelopes will be sent to those participating ICUs with high enrollment rates.

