**Fig. 3 Fig3:**
[figure not shown]
Estimation of samples size calculations based on expected ventilator-free days and mortality. Power analysis has been performed according to Schoenfeld et al [32]. Since we need three probabilities (see Table 1, text highlighted in *yellow*), we have selected three probabilities compatible with our hypothesis (using Mann-Whitney test). We hypothesized that patients in the experimental treatment group have a greater probability of being weaned earlier from the ventilator (0.0641 vs. 0.481) and a lower probability of dying (0.0345 vs. 0.05) for each day of the follow-up period

**Table 1 Tab1:** Calculations for the sample size

	VFDs		Probability of getting off ventilation alive	Probability of death	Probability of receiving ventilation	Expected mortality
	Mean	SD	pa	pd	po	60-day mortality
Control group	9.0	10.7	0.0481	0.0500	0.9019	0.4814
Experimental group	12.0	10.8	0.0641	0.0345	0.9014	0.3308
Difference	3.0		0.0160	-0.0155	-0.0005	-0.1506

*VFD* ventilator-free days, *SD* standard deviation

There will be one single formal interim analysis for both efficacy and futility. This analysis will be performed once 50 % of the planned patients have been randomized and initiated treatment and have been followed up to day 60. To protect against an obvious lack of efficacy, failure to achieve an increase of VFDs ≥ 1 day will justify stopping the trial. To protect against a clear improvement of efficacy, achieving a statistically significant difference in VFDs ≥ 3 days or an absolute difference in 60-day mortality ≥ 15 % (two-tailed significant difference *p* < 0.025) will justify stopping the trial. The interim analysis will be performed at the coordinating center (Hospital Universitario [name], Las Palmas de Gran Canaria, Spain) by an external, independent data and safety monitoring board. Investigators enrolling patients will be blinded to the results of this interim analysis if the stopping rule is not applied.

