### Trial organization

The steering committee is constituted by the study principal investigators who contributed to its design and approved the final protocol (Appendix 2). The executive committee comprises the main investigators of each participating center and is responsible for administrative, trial, and data management. The data and safety monitoring board is composed of external, independent experts in critical care medicine, mechanical ventilation and ARDS, and with the general data provided by three internal members, it will recommend the continuation or discontinuation of the trial based on the data from the interim analysis (Appendix 2). The trial management team comprises a chief investigator, a project manager, a statistician, a clinical epidemiologist, and an investigator expert in clinical trials. The responsibilities of this team are:(i)Planning and conducting the study: designing the protocol, case report forms, designing the investigator manual, and managing and controlling the data quality.(ii)Research center support: assisting the centers with the administrative submission, monitoring recruitment rates, providing sealed randomization envelopes, taking actions to increase patient enrollment, monitoring follow-up, auditing, and sending study materials to the research centers.(iii)Producing a monthly study newsletter (Dexanews).(iv)Programming a research-in-progress meeting every 6 months with principal investigators from all sites.(v)Statistical analysis and research reporting: interim and complete statistical analysis and helping in writing the final manuscript.

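### Fixed blocks of ten held as packs at each ICU, with no placebo described, let staff deduce some upcoming allocations before deciding whom to enrol

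*Protocol article*

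**What the plan says.** The procedure is in the protocol article under Enrollment into the study and randomization. "Randomization will be performed by blocks of ten opaque, sealed envelopes sent to each participating ICU", following a computer-generated random-number table. The ratio is given next: "Randomization will be based on one-to-one allocation of prenumbered envelopes". Resupply uses the same unit: "As requested, a second block of ten sealed envelopes will be sent to those participating ICUs with high enrollment rates". No other block size is mentioned.

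The same section names the arms: "i) conventional treatment without dexamethasone and (ii) conventional treatment plus dexamethasone". No placebo appears anywhere in the article. The only blinding described for investigators, under Sample size calculations and interim analysis, concerns interim results: "Investigators enrolling patients will be blinded to the results of this interim analysis if the stopping rule is not applied".

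Study design gives the scale: "314 patients with persistent ARDS admitted into a network of 18 ICUs from university and community hospitals in Spain". Under Trial organization, the trial management team is responsible for "providing sealed randomization envelopes" to the centers, so the envelopes wait at the ICU.

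**The concern.** An opaque, sealed, prenumbered envelope hides its own content. It does not hide what follows from counting the envelopes already opened. Here the block is the physical pack, its size is the same every time and appears in the published article, and past allocations are visible because the control arm receives no dummy treatment. Towards the end of a pack, staff can work out or guess what remains.

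That matters because enrolment leaves some room for judgement. The qualifying blood gas is taken at minimum rather than fixed FiO2 and PEEP settings. In addition, a patient is excluded if more than 24 hours pass before consent and the results on standard settings are obtained, so delay alone can keep someone out. If foreknowledge influenced who was enrolled, the arms could differ in severity at baseline. Ventilator-free days and 60-day mortality both depend on severity. Intention-to-treat analysis does not repair this, because the selection precedes randomization, and adjustment reaches only measured severity.

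**Working it through.** The article states no figure for predictability, so there is none to reproduce. The check is how much a pack of ten reveals.

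**Inputs**
- Block size 10, ratio 1:1 (Enrollment into the study and randomization).
- 314 patients, 18 ICUs (Study design).
- Assumption: five envelopes per arm in each pack.
- Assumption: staff know all earlier allocations in the pack and guess the arm with more envelopes left, or toss a coin when equal.

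**One completed pack.** With m = 5 per arm there are C(10,5) = 252 equally likely sequences.
- Allocations certain in advance: 2m/(m+1) = 10/6 = 1.67 of 10 (16.7%).
- Correct guesses: m + (4^m/C(2m,m) − 1)/2 = 5 + (1024/252 − 1)/2 = 6.53 of 10 (65.3%). Enumerating all 252 sequences gives the same two results.

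By position in the pack, from the enumeration:

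| Position | Certain in advance | Guess correct |
|---|---|---|
| 1 | 0 | 50% |
| 2, 3 | 0 | 56% |
| 4, 5 | 0 | 60% |
| 6 | 2/252 = 0.8% | 64% |
| 7 | 12/252 = 4.8% | 64% |
| 8 | 42/252 = 16.7% | 72% |
| 9 | 112/252 = 44.4% | 72% |
| 10 | 100% | 100% |

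**Whole trial, every pack used up.** 314 × 0.1667 = 52 allocations certain; guess rate 65.3%.

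**Whole trial, even enrolment.** 314/18 = 17.4, that is 10 ICUs with 17 patients and 8 with 18 (170 + 144 = 314). Each ICU completes one pack and uses 7 or 8 envelopes of a second.
- Certain: 18 × 1.667 + 10 × (14/252) + 8 × (56/252) = 30.0 + 0.56 + 1.78 = 32.3, about 32 of 314 (10%).
- Correct guesses: 18 × 6.532 + 10 × 4.087 + 8 × 4.810 = 117.6 + 40.9 + 38.5 = 196.9; 196.9/314 = 62.7%. Here 4.087 and 4.810 are the expected correct guesses in the first 7 and first 8 positions.

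**Alternative block sizes.** Simulated, each size equally likely, with staff guessing by the running imbalance in the ICU:

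| Block sizes | 20 per ICU | 17 or 18 per ICU |
|---|---|---|
| Fixed 10 | 65.3% | 62.7% |
| 4, 6, 8 | 67.1% | 66.7% |
| 8, 10, 12, 14 | 63.0% | 62.4% |

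Small blocks return to balance more often, so the guess succeeds more often. Larger varied blocks lower the rate only a little. Their main gain is that staff who do not know where a block ends lose the allocations they could be sure of.

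**The case against.** The strongest reply has five parts.

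- **The 5:5 split is not written.** Ten envelopes in a shipment need not be a balanced block. This stands as a caveat. But the article itself calls the pack a block, gives the ratio as one to one and resupplies another block of ten, so 5:5 is the natural reading. The absence of blinding is likewise inferred from the lack of any placebo.
- **The 17% is not a trial-wide average.** This stands. It applies to completed packs; unfinished packs bring it to about 10% under even enrolment, and other enrolment patterns would give other values.
- **Eligibility turns on a measured threshold.** PaO2/FiO2 is assessed on mandatory standard ventilator settings, the exclusions are listed and only consented patients are allocated. This narrows discretion without removing it.
- **Guess rates are not bias.** This stands. A reader might infer that allocation was subverted or that the results will be biased. The article supports neither: it shows an opportunity, most allocations remain uncertain, and no effect on ventilator-free days or mortality can be derived.
- **It is late.** The first patient was enrolled on 28 March 2013, the expected duration is 50 months, and the article appeared on 22 July 2016, about 40 months in. A change reaches few patients. That limits the benefit but does not undo the weakness.

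A reader might also infer that the staff who enrol decide on extubation and could favour one arm there. The article does not say who does what. Any such bias would come from open treatment and would be the same under any block size, so it is no part of this point.

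**Conclusion.** The point holds as a weakness in allocation concealment that the article states outright; it is not a detail left to another document. Assuming 5:5 packs and staff who know past allocations, 1.67 of 10 allocations per completed pack are certain in advance: about 52 of 314 if all packs are used up and about 32 of 314 with even enrolment. The next arm can be guessed correctly about 63 to 65% of the time. The first envelope in a pack is unpredictable, and certainty is confined to the last five positions, mainly the last two. The design permits selective enrolment; whether any occurred cannot be judged from the article. The change should be made for the remaining recruitment, and the patients already enrolled should be checked.

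**What to change.** 1. For envelopes not yet shipped, keep a separate list per ICU but generate it with randomly varied block sizes that include larger blocks, for example 8, 10, 12 and 14. Do not disclose the sizes to sites. Avoid 4, 6 and 8.
2. Ship packs whose size does not coincide with block boundaries, so that the last envelope in a pack is no longer known. Together with the hidden sizes, this is what removes certainty. The guess rate itself stays near 62 to 63%.
3. State whether the packs already shipped were balanced 5:5.
4. For patients already enrolled, compare baseline severity (for example APACHE II, lung injury score and PaO2/FiO2) by arm among those randomized late in a block, say positions 8 to 10, as a sensitivity check. Numbers will be small: with one completed pack in each of 18 ICUs, positions 8 to 10 hold 3 × 18 = 54 patients, plus any from second packs. A difference would be a warning; its absence would not prove that there was no selection.

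Cost: a new computer-generated list, an amendment to the randomization paragraph, and a record of which envelopes came from which list. Arm imbalance within a site may rise slightly. The change protects only the recruitment that remains, about 10 of the 50 planned months counted from publication.

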### Ventilatory management and dexamethasone therapy

Both treatment arms will follow current guidelines for supportive care, including antibiotic therapy. Although patient care is not strictly protocolized, physicians are asked to follow current standards for critical care management. For ventilatory management, enrolled patients in both arms will be ventilated with a V_T_ of 4 to 8 ml/kg PBW, a plateau pressure < 30 cmH_2_O, at a respiratory rate to maintain PaCO_2_ 35 to 50 mmHg and PEEP and FiO_2_ combinations that maintain a PaO_2_ > 60 mmHg or a peripheral capillary oxygen saturation (SpO_2_) > 90 %. Patients in the dexamethasone group will be treated with a daily dose of 20 mg iv from day 1 to day 5 and 10 mg iv from day 6 to day 10. We have selected this dose and time of treatment by doubling the dose used by Meijvis et al [18], since our patients are sicker, and half the dose used by Azoulay et al. [21] to avoid development of neutropenia. Our therapeutic regime is dose-equivalent to that from the Steinberg et al trial [13] with methylprednisolone. Treatment with dexamethasone will be maintained for a maximum of 10 days or until extubation (if occurring before day 10 after study enrollment) (Fig. 1).

